## **2. *Post-intervention qualitative studies* (Timeline 2018/2)**

With a similar recruitment strategy and design to the pre-intervention ones but among participants included in the intervention areas, focus groups/in depth-interviews will be conducted after the intervention is implemented among users to assess the underlying processes determining how communities and individuals change their behaviour or fail to do so.

## **3. *Cost-effectiveness analyses* (WP4: Timelines 2017/4, 2018/4, 2019/3, 2020/2)**

The implementation of the two interventions (user- and health professional targeting) will be costed prospectively during the study period. We will apply the perspective of the health provider, although the time use of volunteer peer support will also be estimated and valued. The observed differences in health seeking behaviour will subsequently translate into differences in screening and case detection rates, which also have cost implications. These will be costed separately based on Diagnoses-related group (DRG) rates. A novel analytical model will be developed to combine the trial data with supplementary information where required, to estimate costs, effectiveness and cost-effectiveness of the two interventions. The model will also be used to assess uncertainty, both overall and for single parameters, and whether the uncertainty has potential to influence policy recommendations.

Equity impact will be considered by combining information about the study outcomes with information about the socio-economic background of the participants. We will utilize both descriptive methods, including quintiles analyses, as well as more analytical approaches that also seek to explain the differences in utilization of cancer screening. The latter include estimation of Gini and concentration indices, i.e. the actual inequity in screening, and parametric decomposition of causal factors.

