#### **A.2.1 The Norwegian Cervical Cancer Screening Program**

The Norwegian Cervical Cancer Screening Program (NCCSP) aims to reduce the incidence and mortality of cervical cancer through identifying and treating early cancer stages, which if left untreated have a high likelihood of progressing to invasive cancer. It was implemented in 1995, and it is based on triennial screening with cytology smears among women aged 25-69. Women with no registered screening test during the last three years receive a reminder letter from the Norwegian Cancer Register with a recommendation to make an appointment with their general Practitioner (GP) to have a smear. Overall, 76% of the women have taken a smear after two reminders [11]. While the letters and reminders raise the attendance for the general population, their effectiveness among immigrants is unknown. The screening programme in Norway does not explicitly target immigrant women and hence they are usually under-recruited and not represented at the population level. Yet another constraint is that the reminders are sent in Norwegian, which might dissuade immigrant women from participating in screening or health intervention programmes. According to the Cancer Registry of Norway, more than half of the women diagnosed with cervical cancer have rarely or never taken a Pap test. The NCCSP is changing the test stepwise in Norway, but the type of test taken by the health professional will not affect the results of our study.

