#### **A.2.2 Immigration and cervical cancer screening**

Cervical cancer is preventable and has a good prognosis if detected early. Although cervical screening has reduced the incidence in many high-income countries, the incidence remains high in countries that do not screen [12]. In accordance to other European countries pointing to low attendance among immigrants, and challenges to access at both the user level and the host health system level [13-15], our research group has newly stated for the first time in Norway that immigrant women, especially from Asia and Africa, are underrepresented in the smears taken at the GP office in Norway [2]. Low attendance to screening programs in turn can result in higher occurrence of cervical cancer in immigrant groups [14] and poor prognoses due to diagnosis at a late stage of cancer, otherwise preventable.

From the *users' point of view*, participation in cervical cancer screening [16] might be influenced by barriers such as fatalistic attitudes, lack of knowledge, fear of cytology smears threatening one's virginity, beliefs that a cytology smear is unnecessary unless one is ill or has risky sexual behaviours, as well as stigmatization within their community and providers [13]. Within the *host health system* barriers such as lack of adequate information for users, language, difficulties in access to health care and varying cultural competence among health workers may prevent new immigrants from following the screening guidelines [17]. However, barriers probably vary among different immigrant groups and in relation to the host country. Therefore, a better understanding of potential cultural, social and other structural barriers to cervical cancer screening programs for different groups of immigrant women in Norway is an essential prerequisite to design culturally appropriate health promotion strategies and screening interventions. The solutions that address these barriers could effectively promote better awareness and encourage women to attend screening, thus diminishing inequity in service utilisation compared to the native Norwegian population.

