### WP2- Heath professional intervention (not included in this application)

A similar process is being used since 2015 to develop the *Heath professional intervention*, but interviewing health professionals. Bergen was divided into 20 clusters according to the 20 geographical subareas defined by Statistics Norway and similar calculations and matched pair randomization to those described above were conducted. All GPs, midwives and private gynaecologists working in the intervention cluster areas will be assigned to the intervention group; similar health professionals working in the other municipalities will be chosen as controls. This intervention will be implemented in Hordaland (Bergen) in autumn 2016 to increase awareness of the health professionals involved in screening working in the chosen municipalities. No change in “screening as usual” will be implemented for health professionals working in the control areas. Our experience in this process will facilitate work related to WP1.

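### WP4 names only DRG rates for pricing extra screening as well as case detection, although the protocol places smears mainly outside hospital

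*Protocol*

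**What the plan says.** The costing plan is in the Protocol, section B.3.2, item 3 (Cost-effectiveness analyses, WP4). It has three parts.

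- **Delivery of the interventions:** "The implementation of the two interventions (user- and health professional targeting) will be costed prospectively during the study period". The viewpoint is given as "We will apply the perspective of the health provider", with volunteer time valued in addition.
- **Consequences of changed behaviour:** the plan expects "differences in screening and case detection rates, which also have cost implications", and the next sentence reads "These will be costed separately based on Diagnoses-related group (DRG) rates".
- **Model:** a model still to be developed will "combine the trial data with supplementary information where required, to estimate costs, effectiveness and cost-effectiveness of the two interventions".

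On where smears are taken, section A.2.1 says that the programme's reminder carries a "recommendation to make an appointment with their general Practitioner (GP) to have a smear". Section A.2.2 reports that immigrant women are "underrepresented in the smears taken at the GP office in Norway". The WP2 section names the professionals it targets: "All GPs, midwives and private gynaecologists working in the intervention cluster areas will be assigned to the intervention group".

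Section B.2 makes incremental cost and incremental cost-effectiveness the outputs of WP4, and the timeline in section 3.1 ends with a comparison and prioritisation of the two interventions.

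**The concern.** DRG rates are, in general use, prices for hospital episodes grouped by diagnosis. They can suit the hospital work-up and treatment of a woman with a pathological test. They are not a natural price for a smear visit in general practice or with another provider outside hospital. Yet the costing sentence covers both.

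An analyst who follows the sentence has two options for the smear visit: find no applicable DRG and enter nothing, or borrow a hospital rate. Either way, a cost that arises with every additional attendance enters the incremental cost at the wrong price. The cost-effectiveness ratios of WP1 and WP2, and total cost in their comparison, inherit the error. The estimated effect on attendance is not touched.

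**Working it through.** The Protocol states no cost figure, so there is none to reproduce. The check is a reading of the text, followed by simple algebra.

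**1. What the DRG sentence covers.** The sentence before it speaks of screening and case detection together. The pronoun that opens the DRG sentence refers to both. Delivery of the interventions is costed in a separate, earlier sentence, so the DRG sentence is the rule for downstream consequences.

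**2. Setting of the priced event.** Sections A.2.1 and A.2.2 place the smear in general practice. The WP2 section adds midwives and private gynaecologists. No section describes the screening smear as a hospital episode, although the outcome register holds smears from any setting.

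**3. Additional women screened in WP1 at the planned effect.**
- Women of screening age in the study area (B.3.1, Participants): 625 + 915 = 1540.
- About half live in intervention clusters: 1540 / 2 = 770.
- Planned increase (Area and sample size): 0.55 − 0.45 = 0.10.
- Additional women screened: n = 770 × 0.10 = 77.

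**4. Error in the ratio.** Let I be the delivery cost, F the cost of follow-up after a pathological test, c the true unit cost of a smear visit with its test, and h the rate applied.
- Correct cost per additional woman screened: (I + F + n·c) / n = (I + F)/n + c.
- As costed: (I + F)/n + h.
- Error per additional woman screened: h − c.
- Error in total incremental cost: n × (h − c) = 77 × (h − c).

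The possible cases are:

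| Rate applied | Error per additional woman | Error in WP1 total |
|---|---|---|
| No DRG applies, h = 0 | −c | −77c |
| h below c | negative | negative |
| h equal to c | 0 | 0 |
| h above c | h − c, positive | 77 × (h − c) |

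The documents give neither c nor h, so the table cannot be turned into money.

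**5. WP1 against WP2.** With the same c and h in both, each ratio shifts by h − c. The incremental ratio between them, with index 1 for WP1, index 2 for WP2 and n₁ ≠ n₂, is (I₁ + F₁ − I₂ − F₂)/(n₁ − n₂) + c, and it also shifts by h − c. The difference in total cost is wrong by (n₁ − n₂)(h − c). So the order of the two on cost per additional woman screened is unchanged, while the level of each ratio and the total costs are not.

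**6. Scale against delivery.** Section 3 requests two half-time assistants for two years of fieldwork: 2 × 0.5 × 2 = 2 person-years. Assuming 1500 to 1750 hours per person-year (not in the documents), this is 3000 to 3500 hours. Assuming 0.5 to 2 provider hours per smear (also not in the documents), 77 smears take 38.5 to 154 hours. The ratio runs from 38.5/3500 = 1.1% to 154/3000 = 5.1%. Test analysis and follow-up are not in the smear hours, and the other project staff are not in the fieldwork hours.

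**The case against.** The strongest reply is that this is a funding-style protocol, that WP4 is a secondary work package with its model still to be built, and that item-level unit costs usually belong in a later economic plan. The clause on supplementary inputs and the promised uncertainty analysis for single parameters leave room for other tariffs. The timeline also schedules cost registration as a separate task. This supports a low severity. It does not remove the point: the clause on supplementary inputs is general, names no tariff for screening, and does not withdraw the specific DRG rule. A later plan would have to depart from that rule to price the visits properly.

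Two narrower replies stand. The Protocol does not define DRG rates, so their hospital character is general knowledge about the term. The outcome register also covers smears from any setting, so the claim is that smears are mainly, not exclusively, taken outside hospital.

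A reader might infer three stronger things that the document does not support:
- **That extra screening is the main resource cost.** Delivery is costed separately, and on the assumptions above the extra smear time is about 1% to 5% of fieldwork time alone.
- **That the cost of screening is left out.** The plan expressly includes it; what is unsuitable is the tariff. A zero price is one possible result, not a certainty.
- **That the choice between WP1 and WP2 would be distorted.** A common error per attendance moves both ratios equally, and the Protocol sets no threshold for either to cross.

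**Conclusion.** The point holds as a minor defect in a stated costing rule. The only tariff named for the extra screening is one for hospital episodes, while the Protocol places smears mainly with providers outside hospital. The error is h − c per additional woman screened, or −c if no DRG applies. It is about 77 × (h − c) in the total incremental cost of WP1 at the planned effect. Sign and monetary size cannot be determined.

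The conclusion rests on three assumptions: that DRG rates carry their usual meaning; that about 770 women live in the WP1 intervention clusters and the planned 0.10 increase is reached; and that one unit cost serves WP1 and WP2. If the mix of providers, and so c, differed between the two, the shifts would differ as well. The Protocol gives nothing from which to size that.

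**What to change.** In B.3.2, item 3, replace the single DRG sentence with one that separates the two consequences:
- Cost smear visits with primary-care or specialist consultation tariffs, according to provider, and the analysis of the test with a test tariff.
- Limit DRG rates to hospital work-up and treatment after a pathological test.
- Use the same unit costs in WP1, WP2 and their comparison.

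The price is a tariff look-up and slightly more costing work. Attendance and test results already come from the screening register. If the type of provider is not available there, the provider mix would have to be assumed and varied in the uncertainty analysis that the plan already foresees.

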### ***B.3.3 Other methodological issues***

#### ***a. Secular trends***

Secular trends, or changes through time disregarding intervention can be a challenge in this type of study. As our outcome measurements rely on linking existing databases, we will include an extended baseline period (from 2012) with repeated measurements of screening attendance several years previous to intervention to better determine the influence of secular trends.

#### ***b. Studying the process and relation with the community***

In addition to the quantitative outcomes, we will examine the process of how our community-based interventions improve health as this information may be just as critical as evaluating the quantitative outcomes.

## **3. The project plan, project management, organisation and cooperation**

This project will take advantage of the on-going collaboration between the Norwegian Minority Health Center (NAKMI) and the Department of Global Public Health and Primary Care at the University of Bergen (UiB), both of which will contribute researchers and facilities. In addition, for the design of the intervention we will collaborate with the NCCSP

and the Norwegian Cancer Society, which has already granted a PhD student ([name]) with one 50% position from 2015 to 2019 in order to develop, implement and evaluate the *Health professional's intervention (WP2)*.

Both NAKMI and UiB are excellent educational environments for researchers and responsible for education of health personnel and dissemination of results to society. NAKMI, headed by its director [name], has broad experience in project administration and collaboration with immigrant communities and is the *Project owner*. [name] (UiB and NAKMI) has extensive expertise in register epidemiology and immigrant health studies in addition to being part time GP at Bergen municipality with extensive contacts among GPs in Norway. She will be the *Project manager*. [name], at UiB, is an expert in health economy analyses and global health. The cross-sectorial cooperation and the interdisciplinarity of the research group hugely increase the feasibility of the study and contribute to further national network building. International partners from Denmark and UK will serve as reference group to additionally ensure the high international standard and quality of our research.

In order to implement the study, we apply the Norwegian Research Council for: WP1 and WP3: three year 100% Post-doc position, two 20% Researcher four year positions (with specific competence on immigrants from Somalia and Pakistan), 50% Communication expert position for the development of the intervention and two 50% bilingual female Project assistant positions (health promoters) for two years to implement the fieldwork. These positions will be located at NAKMI. The post-doc researcher will collaborate with the other members in the design, implementation and evaluation of the User intervention, while the Researchers will additionally focus on WP3 (comparison of intervention). [name] and [name] will be the main responsible for WPs 1 and 3 respectively. At least 6 articles will be published from WP1 and WP3 (see Timeline).

### **3.1 Timeline**

In this Timeline we present the whole project, also parts of the WP2 for better understanding (in cursive means not included in this proposal).

2017

1. Pre-intervention focus groups with Somali and Pakistani women (WP1, Paper 1)

2. Development of User strategy, recruitment and training of peer educators in Akershus/Buskerud from Somalia and Pakistan (WP1, Paper 2)
  3. Implementation User strategy with Somali and Pakistani women (WP1)
  4. Development and registration of cost (WP4)
  5. *Post-intervention Health professional interviews in Hordaland (WP2)*
- 2018
1. Writing papers 1 and 2 (WP1)
  2. Post-intervention interviews in Akershus/Buskerud (WP1, Paper 3)
  3. *Analyses post-intervention register data in Hordaland (2016-2018): attendance to cytology after the Health professional intervention (WP2)*
  4. Cost-effective analyses Health professional intervention (WP4, Paper 1)
- 2019
1. Analyses post-intervention register data in Akershus/Buskerud (2016-2018): attendance to cytology after the User intervention (WP1, Paper 4)
  2. Writing papers 3 and 4 (WP1)
  3. Cost-effective analyses User intervention (WP4, Paper 2)
  4. Comparison of interventions, qualitative approach (WP3, Paper 1)
- 2020
1. Comparison of interventions, quantitative approach (WP3, Paper 2)
  2. Cost-effective analyses: comparison and priority of interventions (WP4, Paper 3)
  3. Dissemination of results to communities, stakeholders and policymakers.

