#### ***Participants***

Women from Somalia and Pakistan are chosen as targets for the *User intervention* following demographic patterns and earlier analyses [2]. All women from these countries living in the intervention areas compose the intervention groups; immigrant women from the same countries of origin living in control areas will be control participants. It is conservatively estimated that 625 and 915 women in screening age from Somalia and Pakistan respectively live in the study area. Approximately half of each part of the women from each country will live in the intervention clusters and will be invited to the study by the bilingual key women through different channels (invitation through the mosque in collaboration with local stakeholders, information at the local shopping centres, snow-ball oral information, etc).

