### Area and sample size

This intervention will be implemented in Akershus and Buskerud. These counties are chosen based on the existence of enough immigrants but avoiding areas known to have low participation rates due to on-going research programs in other health fields. Sample size is calculated for an increase in cancer screening participation from 0.45 to 0.55 with 80% power and 5% significance level. After trying several intra class correlation (ICC) levels, we decided to divide four municipalities in Akershus and Buskerud (Asker, Bærum, Lørenskog and Drammen) in 16 clusters that were matched according to the calculated number of female immigrants aged 20 to 66 from Somalia and Pakistan. To avoid contamination, after assuring that pairs were not naturally linked by a mosque or other natural known gather centre for these populations, clusters will be randomly assigned to intervention or control groups (matched pair randomization) [25].

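### The register window labelled post-intervention for the user intervention (2016-2018) begins at least 12 months before that intervention is delivered, so tests taken before exposure can count as outcome

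*Protocol*

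**What the plan says.** The 2019 entry in section 3.1 (Timeline) of the protocol reads "Analyses post-intervention register data in Akershus/Buskerud (2016-2018): attendance to cytology after the User intervention (WP1, Paper 4". The third item under 2017 in the same timeline is "Implementation User strategy with Somali and Pakistani women (WP1". It follows the pre-intervention focus groups (item 1) and the development of the strategy with recruitment and training of peer educators (item 2). The WP1 text under B.3.1 gives the same order. The numbers after each year are item numbers, not quarters (2017 has five items), so no delivery date is stated.

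On the baseline, B.3.3 a (Secular trends) says "we will include an extended baseline period (from 2012) with repeated measurements of screening attendance several years previous to intervention". No end date is given.

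The parallel study carries the same years, "Analyses post-intervention register data in Hordaland (2016-2018): attendance to cytology after the Health professional intervention", and its start is stated: "This intervention will be implemented in Hordaland (Bergen) in autumn 2016".

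The design target is in the section Area and sample size: "Sample size is calculated for an increase in cancer screening participation from 0.45 to 0.55 with 80% power and 5% significance level". No period is attached to either proportion. B.3.2, item 1, requests the date of every test from the screening register.

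**The concern.** All of 2016, and the part of 2017 taken up by the two preparatory steps, lie before any woman could have been reached. The timeline nevertheless calls the whole of 2016-2018 post-intervention. This is the only outcome window the protocol gives for the main quantitative evaluation of WP1, and no section limits the outcome to tests taken after delivery. The protocol states a window, and that window conflicts with its own schedule, so this is not a detail simply left to an analysis plan.

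Followed as written, a woman tested before delivery is a success in either arm and cannot respond further. Such women add equally to both arms and can shrink the difference. The same months could also be claimed by the baseline, whose end is open.

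WP3 compares the two interventions to guide priorities. If both are read over 2016-2018, the Hordaland intervention has more exposed time than the user intervention, and the comparison would partly reflect the calendar.

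**Working it through.** **Inputs from the protocol.** Proportions 0.45 and 0.55, 80% power, 5% significance (taken as two-sided). Women: "It is conservatively estimated that 625 and 915 women in screening age from Somalia and Pakistan respectively live in the study area", so 625 + 915 = 1540. Allocation: "Approximately half of each part of the women from each country will live in the intervention clusters", so about 770 per arm. There are 16 clusters, so 1540/16 = 96.25 women per cluster. The ICC is not stated.

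**The plan's own figure.** Without clustering, 0.45 versus 0.55 needs 392 women per arm. With 770 available, the affordable design effect is 770/392 = 1.96, that is, an ICC of (1.964 − 1)/(96.25 − 1) ≈ 0.010. With a normal approximation, power is 97.6% at ICC 0, 89.9% at 0.005, 80.3% at 0.01, 63.5% at 0.02 and 37.2% at 0.05. The stated 80% is compatible with an ICC of about 0.01, but cannot be reproduced because the ICC is not given.

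**Share of the window before delivery.** Take the window as 1 January 2016 to 31 December 2018. The earliest delivery in 2017 leaves 12/36 = 33% before exposure; delivery at the very end of 2017 leaves 24/36 = 67%.

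**Illustration of the effect.** Assumptions, none of them in the protocol: a constant testing rate; 45% and 55% are three-year proportions under no exposure and full exposure; any test in the window counts. The yearly rates are

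- λ0 = −ln(0.55)/3 = 0.199
- λ1 = −ln(0.45)/3 = 0.266 (ratio 1.34)

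With t exposed years before the end of 2018:

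- difference in the stated window = 0.55 − exp(−λ0(3 − t) − λ1·t)
- difference counting only tests after delivery = exp(−λ0·t) − exp(−λ1·t)

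The first equals the second multiplied by exp(−λ0(3 − t)), the proportion still untested at delivery. The relative loss from counting pre-exposure tests is therefore 1 − exp(−λ0(3 − t)).

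| Delivery | t (years) | Difference, 2016-2018 | Difference, post-delivery tests only | Loss due to pre-exposure tests |
|---|---|---|---|---|
| 1 Jan 2017 | 2.00 | 6.9 points | 8.4 points (32.9% vs 41.3%) | 18% |
| 1 Jul 2017 | 1.50 | 5.3 points | 7.1 points (25.8% vs 32.9%) | 26% |
| 1 Oct 2017 | 1.25 | 4.4 points | 6.3 points (22.0% vs 28.3%) | 29% |
| 1 Jan 2018 | 1.00 | 3.6 points | 5.3 points (18.1% vs 23.4%) | 33% |

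Against the planned 10 points, the stated window loses 31% to 64% over this range of dates (33% to 67% if the effect is simply prorated by exposed time). Part of that is follow-up shorter than three years, which re-anchoring does not cure.

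**Power.** With the design effect of 1.96 that reproduces 80% for 10 points, the stated window gives 49%, 31%, 24% and 17% for the four dates. Counting only post-delivery tests gives 68%, 59%, 52% and 45%.

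**One-off prompt.** Suppose instead that the intervention prompts a fixed share of the women who would otherwise be untested at the end of 2018. A share of 0.10/0.55 = 18% gives 0.55 × 0.18 ≈ 10 points, wherever in the window delivery falls. Nothing is lost.

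**Hordaland.** Under the constant-rate model with the same effect, a start between 1 September and 1 December 2016 (t = 2.33 to 2.08) shows 8.0 to 7.2 points over 2016-2018, against 6.9 to 3.6 for the user intervention. Equal effects would look unequal.

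**The case against.** The strongest reply is that the quoted line is a work-plan entry in a funding application, not an outcome definition. It speaks of attendance after the user intervention, test dates are requested, and a baseline from 2012 with repeated measurements is planned. The years may only describe the data extract, and the exact window may be fixed in an analysis plan that is not shown. This stands in part: the protocol does not define the outcome as any test in 2016-2018, so the bias is conditional on that reading. It does not remove the contradiction, because nothing in the protocol separates extract from outcome window.

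A second reply is that screening is triennial (section A.2.1), so 2016-2018 is exactly the look-back for having been tested within three years at the end of 2018. A woman tested in 2016 is then rightly counted as covered, and a one-off prompt loses nothing. This is coherent, but the text says post-intervention, not coverage at a date.

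A reader might infer that the effect is diluted by more than half, or that 0.45 versus 0.55 cannot appear in this window. The documents support neither. The first needs delivery after about mid-2017, an effect proportional to exposed time, and any test in the window as outcome; none is stated. It also charges the window with losses that come from short follow-up. The second fails under the one-off prompt.

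**Conclusion.** The contradiction stands on the face of the protocol: at least one third of the window labelled post-intervention precedes the earliest possible delivery in 2017. That conclusion needs only the reading of the label as calendar years.

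The size of any bias is not determined by the documents. If any test in the window counts and the effect works through a constant raised rate, pre-exposure tests take about 18 to 33% of the difference that post-delivery tests would show, depending on the delivery date. If three-year coverage is meant and the effect is a one-off prompt, the loss can be zero. The protocol should say which is meant before outcome data are seen.

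**What to change.** Replace the years 2016-2018 by a window that starts at delivery in each matched pair, gives the control cluster its partner's start date, and runs for a fixed follow-up. Assign earlier tests to the baseline and state where the baseline ends. Adjust or stratify for whether the woman had already been tested within the previous three years, so that women not yet due are not simply scored as failures.

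If three-year coverage at a fixed date is intended, say so and drop the label post-intervention.

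In either case, tie 0.45 versus 0.55 to the chosen window and restate the detectable difference. For WP3, use the same time since delivery in Hordaland, counted from its autumn 2016 start.

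The cost is wording, since test dates are already requested. The downside of the anchored window is a lower control proportion over a shorter period (18 to 33% rather than 45% in the illustration). It does not restore 80% power by itself: the illustration gives 45 to 68%. A longer follow-up would be needed to recover more.
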